### Patient population

In order to be included in the study, potentially eligible patients have to fulfill all of the following inclusion and none of the following exclusion criteria.

#### Inclusion criteria

Able to give written informed consent.At least 18 years of age at time of informed consent signature.Confirmed diagnosis of moderate to severe chronic plaque-type psoriasis diagnosed by a specialist and presence of moderate to severe psoriasis symptoms according to the physician’s clinical judgment at the time of recruitment.Patient is initiating a treatment for psoriasis as per regional policy. This may include secukinumab, other biologics, systemic treatments, and phototherapy. Decision to treat with any of the above-mentioned treatments must have been reached prior to and independently of recruitment in the study.Treatments are prescribed in accordance to the product monograph and regional regulatory and reimbursement policies.Patient is able to understand and communicate with the investigator and comply with the requirements of the study.

### Exclusion criteria

Unwillingness or inability to comply with the study requirementsParticipation in an interventional or non-interventional clinical trial, concurrently or within the last 30 days.

### Study variables

#### Baseline assessments

During the baseline visit, data on patient demographics (age, gender and race), employment, household income, health insurance, medical history and comorbidity are recorded. In addition, a brief physical examination with measurements of height, weight, blood pressure and pulse rate is conducted. The dates of onset of psoriasis symptoms and of psoriasis diagnosis, prior and current psoriasis therapies are also ascertained.

#### Outcome measures

The following outcome measures are to be assessed at each study visit:The incidence of adverse events (AEs).Investigator’s Global Assessment for General Psoriasis (IGA Mod 2011).Psoriasis Area and Severity Index (PASI).Body Surface Area (BSA).Dermatology Life Quality Index (DLQI).Work Productivity and Activity Impairment (WPAI) Questionnaire.Hospital Anxiety and Depression Scale (HADS).Psoriasis Epidemiology Screening Tool (PEST).Health Resources Utilization (HRU) Questionnaire.Psoriasis Symptom Diary (PSD).Treatment Satisfaction Questionnaire.

#### Outcome variables

The primary outcome variable will be the incidence of total AEs, total serious AEs (SAEs) and infections, as measured by the proportion of patients with at least one event, the mean number of events per patient, and the mean number of events per person-year of follow up. All adverse events will be mapped, based on the following hierarchy of exposures (in descending order of priority): [1] secukinumab, [2] other, [3] and non-biologic agents.

The following secondary outcome variables will be used:Physician-Reported Outcomes:Change in IGA from baseline to each visit.Rate of change in IGA for the 5-year follow up duration of the study.Proportion of patients achieving IGA ≤ 1 at any point in time.Time to achieving IGA ≤ 1 during the study follow up period.Durability of effect (IGA ≤ 1).Proportion of patients achieving IGA = 0 at any point in time.Time to achieving IGA = 0 during the study follow up period.Durability of effect (IGA = 0).Change in PASI from baseline to each visit.Rate of change in PASI for the 5-year follow up duration of the study.Proportion of patients achieving PASI 100, 90, 75 and 50 at any point in time.Time to achieving PASI 100, 90, 75 and 50 during the study follow up period.Durability of effect (PASI 100, 90, 75 and 50).Change in BSA from baseline to each visit.Rate of change in BSA for the 5-year follow up duration of the study.Patient-Reported Outcomes:Change in DLQI from baseline to each visit.Rate of change in DLQI for the 5-year follow up duration of the study.Proportion of patients achieving DLQI ≤1 at any point in time.Time to achieving DLQI ≤1 during the study follow up period.Durability of effect (DLQI ≤1).Change in WPAI from baseline to each visit.Rate of change in WPAI for the 5-year follow up duration of the study.Change in the HADS score from baseline to each visit.Rate of change in the HADS score for the 5-year follow up duration of the study.Change in the PEST score from baseline to each visit.Rate of change in the PEST score for the 5-year follow up duration of the study.Distribution of responses to the HRU questionnaire at each visit.Change in HRU from baseline to each visit.Change in the PSD from baseline to each visit.Rate of change in the PSD score for the 5-year follow up duration of the study.Distribution of responses to the patient satisfaction question at each visit.Change in patient satisfaction from baseline to each visit.Proportion of patients adherent to treatment.Other Outcomes:Treatment discontinuation and durability.i.Proportion of patients discontinuing treatment.ii.Reasons for treatment discontinuationiii.Time to treatment discontinuation.iv.Prevalence and incidence of select comorbid conditions, with emphasis on comorbidities associated with psoriasis (e.g. psoriatic arthritis, diabetes, metabolic syndrome, cardiovascular disease)

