**Methods:**

This is a multinational (Canadian and Latin American), prospective, observational study of adult patients with moderate to severe psoriasis that initiate treatment with secukinumab or other approved therapies as per local standard of care. A total of 2500 patients (1250 per cohort) will be recruited in the practices of hospital and community dermatologists. Decision regarding treatment must have been reached prior to and independent of patient enrollment in the study. The study includes a 5-year follow-up with recommended assessments at Baseline, 3 and 6 months post-Baseline, and every 6 months thereafter. The primary objective of the study is safety. Secondary outcome measures relate to effectiveness (Investigator’s Global Assessment -IGA mod 2011-, Psoriasis Areas and Severity Index, Body Surface Area), patient reported outcomes (Dermatology Life Quality Index, Work Productivity and Activity Impairment Questionnaire, Hospital Anxiety and Depression Scale, Psoriasis Epidemiology Screening Tool, Psoriasis Symptom Diary, and Treatment Satisfaction Questionnaire), and healthcare resource utilization.

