### Study design

PURE is a multinational, prospective, observational cohort study conducted in the practices of hospital and community dermatologists in Canada and Latin America (Argentina, Brazil, Costa Rica, Guatemala, Mexico, Panama) that treat patients with moderate to severe chronic plaque psoriasis. [14] Patients with moderate to severe chronic plaque psoriasis whom, prior to and independent of study enrollment, the treating physician has decided to treat with an indicated approved regimen as per standard of care in each participating country.

Patients are followed for up to 5 years from the time of enrollment. In accordance with the observational nature of the study, no assessment visits are imposed for the exclusive purpose of the study, however follow-up visits are recommended at 3 and 6 months post-baseline and every 6 months thereafter. Furthermore, any changes in the management of the patient including, but not limited to, changes in medication dose or frequency, termination of a medication or initiation of a new treatment is at the sole discretion of the treating physician and is to be recorded in the study data collection forms. At any time, patients may be withdrawn from the study by the treating physician or on the patient’s expressed choice.

There are two distinct patient cohorts in the study, those that initiate treatment with secukinumab and those that initiate treatment with other indicated and country-approved therapies as per local standard of care. Given the longitudinal nature of the study, it is anticipated that treatment cohort cross-over can occur. All patients will be followed in the study regardless of and after treatment cross-over, as long as they continue to fulfill the study inclusion and exclusion criteria. All analyses will be based on the intent-to-treat (ITT) principle even though treatment cohort may be considered as a time-dependent variable in some analyses.

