### Statistical analyses

AEs and SAEs will be summarized for the two treatment cohorts using the total number of events, the total number of patients and percentage of patients who experienced at least one event within each body system and within each preferred term of the Medical Dictionary for Regulatory Activities (MedDRA); in these descriptive analyses, crossed-over patients (to either direction) will be described as a separate treatment cohort. Within each treatment cohort, patients experiencing the same event multiple times will be only counted once for the corresponding preferred term and body system. Relative risk/odds and incidence density rate ratio will be estimated to assess the difference between cohorts.

The levels of all physician-reported and patient-reported outcomes will be described for all visits by baseline treatment cohort; between-cohort differences will be assessed using the independent-samples t-test (or non-parametric alternative, as needed) for continuous variables and the chi-square test for categorical variables. In addition, the absolute changes in IGA, PASI, and BSA, will be described and the paired t-test will be conducted to assess the within-group change from baseline at each visit. Multivariate mixed models with repeated measures that may adjust for potential confounders will be used to assess the levels of each of these continuous parameters (IGA, PASI, BSA, DLQI, HADS, PEST, WPAI and PSD) over the five-year follow up period of the study.

For each visit, achievement of therapeutic endpoints, specifically IGA ≤ 1, IGA = 0, PASI 50, 75, 90 and 100 and DLQI ≤1 will be described with the proportion within each treatment cohort. Between-cohort differences will be assessed with generalized estimating equations. Time to achieving therapeutic endpoints, specifically IGA ≤ 1, IGA = 0, PASI 50, 75, 90 and 100 and DLQI ≤1, and the durability of response will be described with the Kaplan-Meier estimator. Between-cohort differences will be described with the log-rank test. Furthermore, Cox’s proportional hazards models that may adjust for potential confounders will be used to compare the two treatment cohorts.

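### Two of the three unranked primary safety measures, and the RR/OR, take no account of follow-up time; the planned person-year rate and rate ratio do, and should lead.

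*Protocol article*

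**What the plan says.** In the Protocol article, Outcome variables lists three measures of the primary outcome, which covers total AEs, SAEs and infections. The first two have no time denominator: "as measured by the proportion of patients with at least one event, the mean number of events per patient". The third does have one: "and the mean number of events per person-year of follow up". The section does not rank the three measures.

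Study design makes observed time variable: "Patients are followed for up to 5 years from the time of enrollment", and "At any time, patients may be withdrawn from the study by the treating physician or on the patient’s expressed choice". No visit is imposed for study purposes. A treatment switch does not end observation: "All patients will be followed in the study regardless of and after treatment cross-over".

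Statistical analyses summarises AEs by counts and percentages of patients, with switchers set apart: "crossed-over patients (to either direction) will be described as a separate treatment cohort". For the cohort contrast, "Relative risk/odds and incidence density rate ratio will be estimated to assess the difference between cohorts". The same section uses Kaplan-Meier and Cox methods for the effectiveness endpoints.

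Sample size considerations rests its precision and detectable odds ratios on proportions of 60%, 5% and 30%. It does not say over what period these apply.

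**The concern.** A proportion of enrolled patients with at least one event depends on how often events occur and on how long patients were watched. When follow-up varies, the crude figure is not a risk over any defined period. Mean events per patient has the same weakness.

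This bears first on the primary aim, which is to describe incidence: a tight interval could surround a figure that is not the 5-year incidence. It bears second on the comparison. If one cohort is observed longer, its crude percentages, RR and OR can look worse with no difference in event rates. Because no measure leads, a reader of the results has no guidance on which to believe when the crude and person-time figures disagree.

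**Working it through.** **Inputs from the article.** 1250 patients per cohort ("A total of 2500 patients (1250 per cohort) will be recruited"); assumed incidences 60% (total AEs), 5% (SAEs) and 30% (infections); maximum follow-up 5 years; detectable ORs 1.30, 1.75 and 1.35 at 90% power.

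**Assumptions, not in the article.** The incidences are read as 5-year risks under complete follow-up. The event hazard is constant and equal in both cohorts. Withdrawal is exponential and non-informative. The article gives no withdrawal rates, so a range is shown.

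**The article's precision.** Half-width = 1.96 × √(p(1−p)/1250):
- 60%: ±2.72% (stated ±3%)
- 5%: ±1.21% (stated ±1.2%)
- 30%: ±2.54% (stated ±3%)

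These reproduce, allowing for rounding up, but they hold for a proportion with no time period attached.

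**Equal retention.** With event hazard λ = −ln(1−p)/5 and withdrawal hazard μ, the expected crude proportion is λ/(λ+μ) × (1 − exp(−5(λ+μ))). Take μ = 0.10 per year in both cohorts, so 1 − exp(−0.5) = 39% have withdrawn by year 5.
- Any AE: λ = 0.1833; 0.1833/0.2833 × (1 − exp(−1.416)) = 0.647 × 0.757 = 0.490, against 0.60.
- Infections: λ = 0.0713; 0.0713/0.1713 × (1 − exp(−0.857)) = 0.416 × 0.575 = 0.240, against 0.30.
- SAEs: λ = 0.01026; 0.01026/0.11026 × (1 − exp(−0.551)) = 0.0930 × 0.424 = 0.039, against 0.05.

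The shifts for any AE (11 points) and infections (6 points) exceed the stated ±3%. The SAE shift (1.1 points) is just under its ±1.2%.

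**Unequal retention, equal hazards.** If a share d has withdrawn by year 5, the formula becomes ln(1−p)/[ln(1−p)+ln(1−d)] × [1 − (1−p)(1−d)]. For any AE with d = 0.20: 0.9163/(0.9163+0.2231) × (1 − 0.32) = 0.5468. With d = 0.50: 0.9163/(0.9163+0.6931) × (1 − 0.20) = 0.4555.

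| 5-year withdrawal | Any AE (60%) | Infections (30%) | SAEs (5%) | Ratio of mean events per patient | Rate ratio |
|---|---|---|---|---|---|
| 30% vs 30% | OR 1.000 | OR 1.000 | OR 1.000 | 1.000 | 1.00 |
| 20% vs 30% | 0.5468 vs 0.5183, OR 1.122 | 0.2707 vs 0.2550, OR 1.084 | 0.0449 vs 0.0421, OR 1.068 | 1.066 | 1.00 |
| 20% vs 40% | 0.5468 vs 0.4880, OR 1.266 | 0.2707 vs 0.2385, OR 1.185 | 0.0449 vs 0.0392, OR 1.150 | 1.145 | 1.00 |
| 20% vs 50% | 0.5468 vs 0.4555, OR 1.443 | 0.2707 vs 0.2208, OR 1.309 | 0.0449 vs 0.0362, OR 1.251 | 1.243 | 1.00 |

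The ratio of mean events per patient equals the ratio of mean follow-up: 4.48 years at 20% withdrawal against 4.21, 3.92 and 3.61 years at 30%, 40% and 50%. Only the any-AE OR at 20% versus 50% exceeds the OR that the article calls detectable for that event type (1.30). At 20% versus 40% it comes close, while the infection and SAE values stay below 1.35 and 1.75 throughout.

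**The case against.** The best answer is that the plan already contains the remedy. A person-year rate is one of the three primary measures, and the incidence density rate ratio is the matching contrast. Under the model above that ratio is 1.00 at any retention. A reader might infer from the first two measures alone that the primary outcome ignores follow-up; the rest of the same sentence shows that it does not. Nor is the rate's third place in the list a defect, since no order of priority is stated.

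A reader might also infer that the cohorts will show false differences because persistence differs between a biologic and a mixed comparator. The article does not support this. It gives no retention figure for either cohort, and leaving a drug is not leaving the study, because follow-up continues after cross-over. Large distortions need large gaps: mean follow-up of 4 versus 3 years gives an any-AE OR of 1.54 in this model, but requires about 37% versus 68% withdrawn by year 5. Comparisons are declared exploratory, with no a-priori hypothesis test.

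Finally, this is a condensed article, and the choice of variance estimator or reporting times commonly sits in an analysis plan.

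All of this stands, and it limits the point. It does not remove the equal-retention result, which concerns description within each cohort and needs no difference in retention. Nor does it settle which measure leads. Follow-up after cross-over closes one route to unequal observation, but tabulating switchers separately may open another: they must stay under observation long enough to switch, so crude percentages across the three groups may cover different spans.

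**Conclusion.** The point holds in a limited form. The crude proportion, mean events per patient and RR/OR are stated choices that mix event rate with time observed, in a study where observed time varies. The primary outcome as a whole does allow for follow-up, through the person-year rate.

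The firmest consequence is descriptive. With any material withdrawal the crude proportion falls short of 5-year incidence, by 11 points for any AE under the assumed 10% per year. The consequence for comparisons is conditional: spurious crude ORs arise only if retention differs. They are modest for a 10-point gap in withdrawal, appreciable for common events at 20 to 30 points, and smaller for SAEs.

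The sizes rest on assumed withdrawal rates, constant hazards and non-informative withdrawal. If event rates fall over time, a plain person-year rate would also shift with retention, which is a reason to report fixed-time incidence beside it.

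**What to change.** - In Outcome variables and Statistical analyses, estimate the proportion with at least one event as cumulative incidence at fixed times, for example 1, 3 and 5 years, by Kaplan-Meier or with death as a competing event, with 95% CIs.
- Name the person-year rate as the lead measure and the already planned incidence density rate ratio as the lead contrast.
- Keep crude percentages, mean events per patient and RR/OR, labelled as descriptive only.
- In Sample size considerations, state the period to which 60%, 5% and 30% apply.

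The cost is a change of analysis wording, a little more analysis work and slightly wider intervals. Each patient's follow-up time is already needed for the person-year rate; cumulative incidence also needs the date of each first event.

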### Primary objective

To describe the long-term safety profile of secukinumab and other indicated therapies in patients with moderate to severe chronic plaque psoriasis.

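### The person-year safety rate counts time off therapy with no exposure-based rate beside it, so it can be diluted and the cohort rate ratio can shift either way

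*Protocol article*

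**What the plan says.** The primary objective (Primary objective) is "To describe the long-term safety profile of secukinumab and other indicated therapies". Outcome variables measures total AEs, SAEs and infections in three ways: the proportion of patients with an event, the mean count per patient, and "the mean number of events per person-year of follow up". Only the third adjusts for time.

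Study design then sets the frame:

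- Analysis principle: "All analyses will be based on the intent-to-treat (ITT) principle even though treatment cohort may be considered as a time-dependent variable in some analyses".
- Duration: "Patients are followed for up to 5 years from the time of enrollment".
- Switching: "All patients will be followed in the study regardless of and after treatment cross-over", provided that the eligibility criteria are still met.
- Stopping: "termination of a medication or initiation of a new treatment is at the sole discretion of the treating physician and is to be recorded" on the study forms. The proportion discontinuing and the time to discontinuation are secondary outcomes.

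Two further provisions bear on exposure. Outcome variables maps each adverse event to a ranked list of exposures (secukinumab, other, non-biologic agents). Statistical analyses shows patients who crossed over as a separate group in the descriptive AE and SAE tables, and also plans an incidence density rate ratio between cohorts.

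**The concern.** The objective concerns the safety of therapies, but the rate describes patients who once started a therapy. A patient who stops and starts nothing else has not crossed over and remains in the initiating cohort. Nothing in the article ends follow-up when therapy stops; the only exit described is withdrawal by physician or patient. That patient's untreated time is added to the cohort's denominator, together with whatever events occur in it.

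For an adverse event that is more frequent on drug, this pulls the cohort's rate towards the off-drug level. The rate ratio then depends on how long each cohort spends off therapy as well as on the on-drug rates. The article provides no second rate that would let a reader separate the two.

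**Working it through.** **The plan's own figures.** The article states no person-year rate and no precision for one. Its precision figures in Sample size considerations concern proportions with n = 1250. The half-width 1.96 × √(p(1−p)/1250) gives 2.7 points at 60%, 1.2 at 5% and 2.5 at 30%, which agree with the stated 3, 1.2 and 3 at the article's rounding. They do not depend on this point.

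**Does any provision take untreated time out of the denominator?**

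- The time-dependent cohort is permissive, applies to some analyses, and is not tied to the primary rate.
- The exposure ranking allocates events. It has no level for no therapy, and no matching rule for person-time is given.
- The crossed-over group covers moves between the two cohorts. It does not cover a patient who stops without switching cohort.

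So for this last group the stated denominator stands.

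**Effect on one cohort's rate.** Let u be the untreated share of follow-up. Then

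reported rate = (1 − u) × on-drug rate + u × off-drug rate.

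The share of the on-drug excess that is lost equals u. Assumed rates (not in the article): 0.20 per person-year on drug, 0.10 off drug.

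| u | Calculation | Reported rate |
|---|---|---|
| 10% | 0.9 × 0.20 + 0.1 × 0.10 | 0.19 |
| 20% | 0.8 × 0.20 + 0.2 × 0.10 | 0.18 |
| 30% | 0.7 × 0.20 + 0.3 × 0.10 | 0.17 |

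If events after stopping were mapped away from the cohort while their person-time stayed, the second term would vanish and the rates would be 0.18, 0.16 and 0.14. The article does not say that this will happen; it does not exclude it either.

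**How large might u be?** Assume a constant stopping hazard over 5 years, with a fraction S still on the initial drug at year 5. The share of follow-up on that drug is f = (1 − S)/(−ln S).

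- S = 80%: f = 0.20/0.223 = 0.90, so 10% of follow-up is off the initial drug.
- S = 50%: f = 0.50/0.693 = 0.72, so 28% is off it.

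Some of that time will be spent on a replacement drug, so 10% and 28% are upper bounds on u for those values of S.

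**When is there dilution?** With r = off-drug rate ÷ on-drug rate, reported ÷ on-drug rate = f + (1 − f)r, treating all time off the initial drug as untreated.

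| r | S = 80% | S = 50% |
|---|---|---|
| 0 | 0.90 | 0.72 |
| 0.5 | 0.95 | 0.86 |
| 1 | 1.00 | 1.00 |
| 1.25 | 1.03 | 1.07 |

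Dilution requires r below 1.

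**Effect on the rate ratio.** The comparator is active therapy, so both cohorts are affected. Assumed off-drug rate 0.10 throughout.

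- On-drug rates of 0.20 in both cohorts (true ratio 1.00), u = 10% and 30%: 0.19/0.17 = 1.12. With the shares reversed, 0.17/0.19 = 0.89.
- On-drug rates of 0.20 and 0.16 (true ratio 1.25), u = 30% in both: 0.17/0.142 = 1.20.
- The same rates, u = 30% and 50%: 0.17/0.13 = 1.31.

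The ratio can move down, up, or away from 1.00 when there is no true difference.

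**The case against.** The strongest reply is that a condensed article need not settle risk windows, lags or the matching of person-time to exposure; those are usual content of an analysis plan, and one may exist. The safety analysis is also not purely ITT: it has the exposure ranking, the crossed-over group and the time-dependent option. This stands in part. The absence of a lag or window is not the point here. The point is that the article does name a denominator and an analysis principle for a primary measure, and neither the ranking nor the crossed-over group reaches a patient who stops without switching.

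A second reply is that all-follow-up time is a legitimate registry estimand. It captures late events, and it avoids informative censoring when patients stop because of emerging problems. This stands, and it is a reason to keep that rate. A reader might infer that it should lose its primary status; the article does not support going so far, because its objective is long-term safety and each rate answers a fair question.

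A third reply is that the consequence is limited. Two of the three primary measures use no person-time, the sample size rests on proportions, and cohort comparisons are declared exploratory. This also stands. It limits the weight of the point, but the descriptive rate itself is still affected.

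**Conclusion.** The point holds in a limited form. The stated denominator mixes treated and untreated time for patients who stop without switching cohort, and no mandatory provision separates the two. For events with a higher rate on drug than off, the cohort rate is diluted in proportion to the untreated share: 0.19 to 0.17 against 0.20 under the assumed rates and 10% to 30% untreated time. The rate ratio can be biased either way if that share differs between cohorts.

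This rests on three assumptions: the on-drug and off-drug rates, the untreated share, and that patients who stop remain in follow-up. The last follows from the absence of any rule ending follow-up at that time. The article gives no figure for the first two.

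Two stronger readings are tempting. One is that the ITT rule hides risk as such. It does not where off-drug and on-drug rates are equal, and the reported rate is too high where the off-drug rate is higher. The other is that the ratio must shrink, for instance from 2.0 to 1.5 at 50% untreated time (0.15/0.10). That calculation needs an unaffected comparator, whereas the comparator cohort receives other biologics, systemic treatments or phototherapy, and nothing in the article supports a 50% share.

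**What to change.** In Outcome variables and Statistical analyses, add an exposure-based rate beside the all-follow-up ITT rate: events from start to stop of the therapy plus one pre-stated lag, divided by person-years in the same window, with untreated time shown as its own category. Estimate the incidence density rate ratio on both. In Study design, state that safety rates are not restricted to the ITT principle.

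The change is to analysis wording only, because starts and stops of treatment are already recorded. The exposure-based rate rests on fewer person-years, so its intervals are slightly wider. A lag must be chosen in advance. Stopping may be informative, and late events may fall outside the window, which is why the all-follow-up rate is kept.
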